# Co-STARS: a feasibility evaluation of a co-produced mental health literacy training package to reduce mental health inequities for Black young people in underserved communities – study protocol for a randomised controlled trial with an external pilot, process evaluation and economic analysis

**DOI:** 10.1136/bmjopen-2025-103120

**Published:** 2026-03-18

**Keywords:** MENTAL HEALTH, PUBLIC HEALTH, Pragmatic Clinical Trial, Feasibility Studies, Health Equity

## Abstract

**Introduction:**

Severe mental illness such as psychosis is among the most disabling illnesses worldwide, disproportionately affecting minoritised ethnic groups and those in socioeconomic disadvantage. In the UK, people from Black ethnic backgrounds are more likely to experience a first episode of psychosis and to be detained under the Mental Health Act than White British people. There is a clear need for mental health services to improve cultural awareness and understanding of the broader social needs of minoritised groups, as well as the need to improve mental health literacy (MHL) within Black communities to empower individuals to seek timely mental health support. This protocol describes our programme of work which aims to assess the feasibility, acceptability and cost-effectiveness of Co-STARS, which is a co-produced, culturally appropriate tiered training package.

**Methods and analysis:**

We co-produced a culturally appropriate, place-based, tiered MHL training package (Co-STARS) to deliver within underserved Black communities and via an e-learning package implemented among staff within mental health trusts. The training will be evaluated in stages. First, a pilot cluster randomised controlled trial will assess the feasibility and acceptability (defined as participants’ perceptions of the training’s relevance, usefulness and delivery) of a lived experience-led MHL training package delivered by Black young people with experience of mental ill health, to underserved communities in Birmingham, UK. Acceptability will be quantified through participation and completion rates and explored qualitatively via focus groups and interviews. Second, a stepped-wedge cluster randomised trial will evaluate the feasibility of an e-learning training programme for mental health professionals. We will embed a process evaluation to explore change mechanisms and identify barriers and enablers for future implementation. Third, we will use realist-informed participatory systems mapping and novel epidemiological analyses to explore downstream effects (ie, improved care access for Black ethno-racial groups within the intervention areas). Last, a cost-effectiveness framework will be developed to assess whether the intervention is good value for money in future efficacy trials. In the cluster trial, eight clusters will be randomised to the intervention arm (face-to-face training in the community) and control arm (display of MHL materials) with pre- and post-assessments in 120 participants from 8 clusters, 3 weeks apart. In the stepped wedge trial, six clusters (clinical teams within NHS mental health trusts) including 120 NHS staff in total, will move from control phase to intervention phase in a stepped wedge manner, with pre-assessments and post-assessments.

**Ethics and dissemination:**

This proposal was reviewed by the Research Governance of the University of Birmingham and UK Research and Innovation (UKRI) grant reviewers. Ethics approval was granted by East of Scotland Research Ethics Service. The findings will be communicated in research conferences, stakeholder meetings, via social media, through publication in peer-reviewed journals and as a policy document.

**Trial registration number:**

ISRCTN10517405.

STRENGTHS AND LIMITATIONS OF THIS STUDYThe trial intervention was co-produced by Black young people with lived experience of mental ill-health, creating a culturally appropriate, place-based, tiered mental health literacy training package delivered by young people.Utilises a two-pronged approach aimed at improving culturally responsive care among NHS staff and enhancing mental health literacy among Black communities.Employs a pilot cluster randomised controlled trial and a pilot stepped-wedge trial design.Limitations of e-learning interventions include superficial learning and a lack of peer or interactive learning.Community-based training has limitations including participants’ proficiency with the English language.

## Introduction

### Background and rationale

 Severe mental illnesses (SMI) such as psychosis are among the most disabling illnesses worldwide.^1^ They are accompanied by enormous personal, healthcare and societal costs and disproportionately affect minoritised ethnic groups and those in socioeconomic disadvantage.^2 3^ Within the UK, people from Black ethnic backgrounds (African, Caribbean and British) are three to five times more likely to experience a first episode of psychosis (FEP) and are more likely to be detained under the Mental Health Act than White British people.^4^,^7^

Factors contributing to these disparities are complex and influenced by wider inequities within and beyond health systems, including bias, discrimination and racism towards Black individuals, as well as stigma and lack of recognition of the symptoms of mental illness.^8^,^10^ Further barriers to accessing timely care include internalised and externalised stigma, differing illness attributions and a disinclination to access mental health services and primary care, with a preference to seek help from faith-based or community organisations.^11^,^13^ This lack of trust and disengagement in services is thought to stem from feelings of disempowerment within the system, perpetuated by negative experiences and relationships with health professionals including experiences of racism, cultural insensitivity and care with diminished autonomy.^14^,^18^ Black individuals with psychosis are less likely to be offered National Institute for Health and Care Excellence (NICE) recommended treatments such as clozapine for treatment-resistant schizophrenia^19^,^21^ or cognitive behavioural therapy,^22^ but are more likely to be prescribed depot antipsychotics, re-admitted to hospital and to have longer inpatient stays.^19 23^ The consequences of these experiences are likely to be far-reaching, with recent work showing poorer 5-year clinical and social outcomes for those from Black backgrounds with FEP.^24^

Health literacy refers to an individual’s ability to understand and use information to make decisions about their health and navigate health services.^25 26^ It is described by the WHO as the cornerstone of a healthy society, with health literate individuals more likely to actively participate in societal economic prosperity, community activities and enjoy better health and well-being.^26^ Low levels of health literacy, often observed in individuals from lower socio-economic backgrounds, minority ethnic groups or those affected by mental health conditions, the groups already facing significant health inequities,^25 27^ are recognised by the WHO as being one of the most influential social determinants of health.^25 26 28 29^ With rising poverty in the UK, coupled with an increased prevalence of mental health difficulties, particularly in young people,^15 30^ addressing these issues has never been more pertinent.

Mental health literacy (MHL) refers to having the necessary skills, knowledge and agency to aid in the recognition, management and prevention of mental illness.^31^ MHL is essential for promoting early detection and early treatment of mental health problems to improve longer-term outcomes.^32^,^34^ In large-scale programmes that seek to reduce mental health stigma, interventions developed and delivered by people with lived experience of mental health conditions were the most effective.^35 36^ Thus, there are calls for MHL interventions to be developed and applied so that they fit the context in which they are to be deployed, and that high priority groups are engaged through co-design principles.^26 37^ To date, there is no evidence of effective MHL interventions delivered by (and for) high priority, marginalised groups, with research in this area limited to low-quality studies and lack of rigour to establish efficacy.^3538^,^41^

### Co-STARS: a co-produced training package

Building on the findings from Phase 1 of the Co-STARS programme (2023–2024), which involved the co-production of the training package with Black African and Black Caribbean young people with lived experience of mental ill health, we will conduct a feasibility evaluation of a co-produced, culturally appropriate, place-based MHL training package (Co-STARS) delivered within underserved communities across Birmingham, UK, and via an e-learning package implemented within two large mental health trusts serving these communities. Birmingham is a large multi-cultural city with numerous risk factors indicative of low levels of health literacy. 51% of the population consists of individuals from ethnic backgrounds, with 9% from Black African and Black Caribbean heritage (compared with 3.5% as national average).^42^ Approximately half of Birmingham wards fall within the most deprived decile of the English Index of Multiple Deprivation, indicating that these areas are among the top 10% of neighbourhoods nationally with the highest levels of social and economic disadvantage.^42^ The combined effects of deprivation and minority status are reflected in the high estimated incidence of psychosis in Birmingham, with approximately 431.2 new cases per 100 000 young people aged 16–35 years annually, of which around 75% occur among individuals from ethnic minority backgrounds, according to modelled forecasts from PsyMaptic-A.^43 44^ Birmingham is also one of the most vulnerable areas to literacy challenges in the entire country.^45^ These highlight the importance of addressing MHL in settings such as Birmingham to address place-based health inequities.

By strengthening both community MHL and professionals’ cultural responsiveness, Co-STARS seeks to improve recognition of emerging symptoms, reduce stigma and mistrust and promote timely help-seeking. Over time, these mechanisms are expected to contribute to earlier access to care, reduction in crisis presentations and better recovery trajectories among Black young people at risk of psychosis. Indicators of success in this feasibility phase include improvements in mental health knowledge, stigma reduction and help-seeking efficacy (WP1) and enhanced multicultural competence among professionals (WP2).

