**Figure 1 F1:**
[figure not shown]
Phased approach to Co-STARS evaluation. This figure outlines the three planned phases: Phase 1 (co-production of MHL training), Phase 2 (feasibility evaluation) and Phase 3 (definitive multi-site trial). MHL, mental health literacy; RCT, randomised controlled trial; UKRI, UK Research and Innovation.

The following outputs from the first phase will now be evaluated in phase 2:

Lived experience-led training package delivered by young people within Black diaspora communities (evaluated as part of WP1).e-learning on culturally responsive care for mental health professionals (evaluated as part of WP2).

We will pilot the feasibility of the training outputs through a series of evaluations (figure 2), which will form the basis for our Phase 2 activities (figure 1). If we demonstrate acceptability and feasibility of the training package, we will seek funding to progress to Phase 3, which is a multi-site (across all four nations in the UK) large scale cluster randomised controlled trial (CRT).

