## Methods and analysis

Trial status: Phase 2 trial recruitment started in March 2025 and is due to conclude in January 2026.

Phase 2 aims: We aim to undertake a pilot evaluation assessing the feasibility, acceptability and cost-effectiveness of a MHL package designed to promote equitable mental healthcare access and improve outcomes for underserved groups. We co-designed and co-developed the following work packages (WP; figure 2) based on close engagement with stakeholders and patient and public involvement and engagement (PPIE) :

WP1: Pilot CRT of lived experience-led MHL training in community settings.WP2: Pilot Stepped Wedge Cluster Randomised Trial (SWCRT) of e-learning for mental health professionals.WP3: Mixed-methods study: Systems mapping and systems change evaluation.WP4: Economic evaluation of WP1-3 to develop a framework to examine cost-effectiveness and social return on investment (SROI).

In addition to assessing impact, we will embed a mixed-methods realist-informed process evaluation to explore the mechanisms of change and resources required to support intervention reach and impact in the continued rollout. We will develop theories that explain how outcomes targeted by Co-STARS are achieved, for whom, why and under what circumstances (contexts). The process evaluation will comprise targeted searches for literature, using the principles of a realist synthesis, interviews with various groups of stakeholders and a document review. The process evaluation will be critical to understand how the implementation is achieved, how each of the interventions produces change and how context might affect implementation and outcomes, including impact on mental health inequalities. Although effectiveness will not be tested at this stage, a pilot randomised design is essential to evaluate feasibility of recruitment, randomisation, data collection and implementation procedures of this intervention. These feasibility outcomes will determine whether progression to a definitive multi-site effectiveness trial is justified and inform its design.

A completed SPIRIT 2025 checklist is provided as online supplemental material 1, detailing the corresponding page and line references within this protocol.

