Sample size: We will recruit 120 participants from the eight randomised clusters. Formal power calculations are not necessary as no hypothesis testing for trial effectiveness is being evaluated.^55^ A sample of 120 (with ~60 per arm) meets sample size recommendations for pilot and feasibility studies and is sufficient to provide precision of feasibility parameters and estimates of study summary measures for a definitive trial.^56^ 20 participants in total will be recruited for focus groups (three groups of five diverse participants) and five 1:1 interviews.

Analysis: Descriptive statistics will be used to assess training fidelity and feasibility outcomes. Other data will be analysed using thematic analysis to generate important themes and patterns.^57 58^ For the secondary outcomes, means, CIs, intra-cluster correlation coefficient (ICC) of the outcome measures (both within-study and between-study clusters) will be estimated to determine which outcome(s) are most sensitive to change and provide sample size calculation for definitive trial.

ICCs for each quantitative outcome will be estimated using mixed-effects regression models including a random intercept for clusters, following the approach recommended by Hemming *et al* for cluster and stepped-wedge feasibility studies.^59^ Analyses will be undertaken in Stata (V.18). The ICC estimates, along with observed variances and completion rates, will inform the design of the definitive trial by (i) identifying outcomes that are most sensitive to change and (ii) providing parameter estimates for sample size and power calculations.

Missing data will be assessed for extent and pattern. The proportion of missing values for each variable will be reported, and exploratory analyses will assess whether missingness appears random or systematic. As this is a feasibility study, no formal imputation will be undertaken for primary feasibility outcomes; however, simple sensitivity analyses using mean or regression-based imputation may be conducted to evaluate the potential impact of missing data on secondary outcomes.^55 56^ The findings will inform strategies for minimising and handling missing data in the future definitive trial.

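### Score improvement is listed as a sign of success in a phase that does not test effectiveness, and eight clusters cannot reliably show which WP1 scale is most sensitive to change

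*Protocol article*

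**What the plan says.** In the introduction, the section on the co-produced training package ends its account of expected mechanisms with: "Indicators of success in this feasibility phase include improvements in mental health knowledge, stigma reduction and help-seeking efficacy (WP1"), followed for the staff component by "enhanced multicultural competence among professionals (WP2"). No threshold, comparator or degree of certainty is attached to improvement.

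The rest of the article takes a different line:
- Project phases (text after Figure 1): "If we demonstrate acceptability and feasibility of the training package, we will seek funding to progress to Phase 3".
- Methods and analysis, Phase 2 aims: "Although effectiveness will not be tested at this stage", and then "These feasibility outcomes will determine whether progression to a definitive multi-site effectiveness trial is justified and inform its design".
- WP1, Sample size (the same statement is made for WP2): "Formal power calculations are not necessary as no hypothesis testing for trial effectiveness is being evaluated".
- WP1 and WP2, Outcome: the questionnaire scales are secondary.

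The WP1 Analysis section mentions sensitivity to change twice. The first mention says that means, CIs and ICCs will be estimated in order to determine which outcomes have it and to supply the Phase 3 sample size. The second says that ICCs, observed variances and completion rates will inform the definitive trial by "identifying outcomes that are most sensitive to change" and by providing parameters for sample size and power.

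**The concern.** Two readers of this article could judge the same results differently. One, following the introduction, would call the phase successful because scores rose, or disappointing because one fell. The other, following the methods, would look at cluster consent, uptake, completion, retention and acceptability and give the scores no weight. The absence of a power calculation is justified only under the second reading.

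The WP1 use of the estimates raises a related problem. With four clusters per arm, differences between scales in apparent change are largely sampling error. An outcome chosen because it seemed to move most may not be the most responsive one, and its observed change will tend to overstate the truth.

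**Working it through.** **Plan's own figure.** WP1 has 120 participants in 8 clusters allocated 1:1. 120/8 = 15 per cluster and 4 × 15 = 60 per arm, which agrees with the article's figure of about 60. It gives no effect size, SD, ICC or power to reproduce.

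**Inputs from the article.** 4 v 4 clusters; four WP1 scales (one knowledge, two stigma, one help-seeking); one WP2 scale.

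**Assumptions (not in the article).** 15 per cluster with no loss; ICC 0, 0.05 or 0.10; correlation between scale estimates 0 to 0.7; baseline–follow-up correlation r = 0 (unadjusted) or 0.6 (adjusted); approximately normal estimates.

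**Step 1: precision.** The standard error of a standardised difference between arms is

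SE = √[2 × (1 + 14 × ICC)/60] × √(1 − r²).

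The 95% CI half-width uses t on 6 df.

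| ICC | SE, unadjusted | SE, r = 0.6 (× 0.8) | Half-width, unadjusted |
|---|---|---|---|
| 0 | √(2/60) = 0.183 | 0.146 | 0.45 SD |
| 0.05 | √(3.4/60) = 0.238 | 0.190 | 0.58 SD |
| 0.10 | √(4.8/60) = 0.283 | 0.226 | 0.69 SD |

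**Step 2: improvement when the training does nothing.** Each scale has a 0.5 chance of moving favourably, whatever the SE. For four independent scales, P(at least one) = 1 − 0.5⁴ = 0.94 and P(all four) = 0.5⁴ = 0.06. With correlated scales (400,000 simulated trials):

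| Correlation | At least one of four | All four |
|---|---|---|
| 0 | 0.94 | 0.06 |
| 0.3 | 0.86 | 0.14 |
| 0.5 | 0.80 | 0.20 |
| 0.7 | 0.73 | 0.27 |

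For the single WP2 scale the chance is 0.50. Uncontrolled pre–post change would be weaker evidence still, because time and repeat-testing effects would add to chance.

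**Step 3: finding the responsive scale.** Let one scale truly change by 0.4 SD and three by 0.2 SD. The right one shows the largest observed change in 46% of trials at the worst corner (ICC 0.10, correlation 0, unadjusted) and in 91% at the best (ICC 0, correlation 0.7, adjusted). At ICC 0.05 and correlation 0.3 it is 55% unadjusted and 63% adjusted.

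**Step 4: the apparent size of the best-looking scale.** If all four truly change by 0.2 SD, the expected largest estimate is 0.2 + c × SE, where c is the mean of the largest of four standard normals: 1.03 at correlation 0 and 0.56 at 0.7.
- Upper end: 0.2 + 1.03 × 0.283 = 0.49 SD.
- Lower end: 0.2 + 0.56 × 0.146 = 0.28 SD.

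**The case against.** The introduction's sentence is an open list in a programme-theory paragraph, with no threshold and no consequence attached. The operative sections consistently tie progression to feasibility and acceptability. A reader might infer that a go decision can rest on chance movement in scores, but no section links the score improvements to a go or stop decision, so the documents do not support that. What remains is two incompatible descriptions of success.

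A reader might also infer that the plan ranks scales and picks the one with the largest change. No such rule is written. The second WP1 statement lists ICCs, variances and completion rates, not observed effects, and sensitivity to change could mean responsiveness of an instrument. This stands in part. However, the first statement does name means and CIs as the basis, the term is not defined, and any judgement of responsiveness from these eight clusters has the imprecision shown above.

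Nor does any section say that the pilot's observed difference will become the Phase 3 target difference. The inflation in step 4 is a risk to close off, not something the plan commits to.

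The at-least-one criterion is not in the article either, and its list of domains could be read as requiring all of them. That is why both probabilities are shown. Reporting means, CIs and ICCs is proper in a pilot and is not criticised here. Numeric progression bands are a separate matter that a condensed article may leave to the full protocol.

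**Conclusion.** The point holds as an internal contradiction plus a use of the WP1 estimates that the design cannot support. Without a threshold, improvement on at least one WP1 scale would appear in 73–94% of trials of a training with no effect, and on all four in 6–27%. The more responsive scale would look best in 46–91%, and the best-looking scale would average 0.28–0.49 SD against a true 0.2 SD.

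These ranges rest on the assumed ICCs, correlations, baseline adjustment and true effects. The correct-pick rate is the most sensitive to them: its upper end needs an ICC near zero, highly correlated scales and baseline adjustment together. The qualitative conclusions, that chance readily produces improvement and that the best-looking scale overstates its effect, hold in every scenario. The point should be corrected, but it does not invalidate the feasibility aims.

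**What to change.** - **Introduction, co-produced training package section:** replace score improvement as an indicator of success with the feasibility and acceptability outcomes already listed under WP1 and WP2 (cluster consent, uptake, completion of measures, retention, acceptability). State that score changes are descriptive, reported with CIs, and have no bearing on success or progression.
- **WP1 Analysis:** choose Phase 3 outcomes on completion, floor and ceiling effects, variance and ICC, and relevance to stakeholders, not on the size of observed change.
- **WP1 Analysis:** state that the Phase 3 target difference will be set on importance and not taken from the pilot estimate.

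No new data or participants are needed. Recruitment was due to end in January 2026, but the change affects only interpretation and the choice of outcomes, so it can still be made. The small downside is that the pilot could not be reported as successful because scores improved.
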